**Fig. 1 Fig1:**
[figure not shown]
Schedule of enrolment, interventions, and assessments

Data collection will occur at five different time points (baseline, post-intervention, 6-months, 12-months, and 24-months) for patients in both groups. Baseline testing will be completed after enrollment and prior to starting the assigned intervention. Patients will begin the intervention within one week of completing baseline testing. Post-intervention testing will occur within one week of completing the assigned rehabilitation program. Follow-up measures will be repeated longitudinally at approximately 6, 12, and 24 months after baseline testing (Fig. 1). A description of the specific outcomes associated with each of these aims is presented below. If any patients are unable to complete the follow-up sessions in person, the outcomes assessments for Aims 1 and 3 will be collected electronically to reduce attrition.

### Interventions

Patients in both the FIRE and SOC groups will complete two supervised and three unsupervised sessions during each week of the 6-week intervention, for a total of 12 supervised rehabilitation sessions and 18 unsupervised rehabilitation sessions. During the supervised sessions, patients will work directly with a credentialed rehabilitation specialist (physical therapist or athletic trainer) who was trained on the intervention procedures and demonstrated proficiency during prerecruitment calibration. The treating clinicians will schedule rehabilitation sessions with patients and record the date, duration of session, and exercises completed during each supervised session. Additionally, the treating clinician will record any reports of patient soreness, discomfort, or other symptoms and adjust the intervention consistent with the tenets of evidence-based practice. Patients will be instructed on how to complete the unsupervised exercises after the initial supervised session and will demonstrate the home exercises to the treating clinician before leaving the clinic to help ensure full understanding. To track compliance with unsupervised sessions, patients will be provided an exercise program and log to record the number of sessions, sets, and repetitions of exercises completed. Patients will be asked to demonstrate the exercises performed at home to assess recall and technique during each subsequent supervised session. Patients with reported non-compliance, limited recall, or reported displeasure with performance of the assigned exercises will be retrained and encouraged to continue with the allocated interventions. The treatment course will be modified (and annotated) as required based on the needs of the patient, treatment response, and patient preference. The home and supervised exercise library for both the SOC and FIRE programs have been included as supplements.

### Standard of care rehabilitation program

Details of the SOC exercise program are provided in the supplemental material (Standard of Care Supervised and Home Exercise Intervention Protocols). The supervised portion of the SOC will contain previously established balance training exercises, progressive 4-way (inversion, eversion, dorsiflexion, plantarflexion) ankle strengthening program using resistance bands [39–41], hip strengthening program using resistance bands and rotational movements, talocrural joint mobilization, and triceps surae stretching [23]. This combination of treatment exercises represented the most common rehabilitation techniques for CAI and was developed based on previous clinical trials [23, 41–43]. These exercises were recommended in a recently published clinical practice guideline for assessment and treatment of ankle sprains and instability [44].

The evidence-based dynamic balance training exercises include: (1) single-limb static balance, (2) single-limb hops to stabilization, (3) hop to stabilization and reach, and (4) unanticipated hop to stabilization. Static balance exercises will include single-limb stance with eyes opened and closed on firm and foam surfaces. Starting points will be individually determined, but the performance-based progression for each exercise will follow a previously established protocol [42]. Strengthening exercises for dorsiflexion, plantar flexion, inversion, and eversion of the ankle and flexion, extension, adduction, and abduction of the hip will be completed using resistance bands [40, 41, 43]. Patients will use a heavy band during the first two weeks, an extra heavy band during the middle two weeks, and a special heavy band for the last two weeks of the intervention [41]. The number of sets and repetitions completed during each treatment session will be progressed based on a previous protocol [41]. Finally, to address range of motion, patients will receive talocrural joint mobilization, triceps surae stretching, and wobble-board training. Joint mobilizations will consist of two, 2-min sets of Maitland Grade III anterior-to-posterior talocrural joint mobilizations with 1-min of rest between sets [45]. The triceps surae stretching will consist of three sets of 30-s of stretching with the knee in full extension as well as three sets with slight knee flexion to target the gastrocnemius and soleus muscles [46]. Range of motion will also be targeted using a progressive wobble board protocol, which will progress from sitting, double limb stance, and single limb stance. The unsupervised sessions for the SOC protocol will consist of components extracted from the supervised rehabilitation session including single-limb balance, resistance band, and triceps surae stretching exercises.

### Foot intensive rehabilitation program

Details of the FIRE intervention can be found in the Additional file 1 (FIRE Supervised and Home Exercise Intervention Protocol). The FIRE intervention will include the progressive balance training, ankle and hip strengthening, and range of motion exercises from the SOC intervention; however, several exercises will be modified and added that concentrate on foot muscle activation, plantar cutaneous somatosensory feedback, and the integration of foot stability during movement. Plantar massage will consist of two, 1-min plantar massages with a 1-min rest between sets. This massage will be a combination of effleurage and petrissage techniques to the entire plantar aspect of the foot with the patient supine [28]. Four previously established exercises will target the IFMs including the short-foot, toe-spread-out, hallux extension, and lesser-toe extension [31, 32, 47]. In the first treatment session, patients will start each exercise in a seated position. Progression to double-limb stance and single-limb stance will occur when an exercise is done correctly for an entire session without compensation. A series of exercises will also target the extrinsic foot muscles involved in foot posture including resistive band supination and pronation, step ups with active supination or pronation and bilateral heel raises with a ball squeeze between the heels [48, 49]. The balance training exercises described for the SOC intervention will be completed during the FIRE intervention; however, the FIRE group will be instructed by the supervising interventionist to emphasize IFM activation during static balance exercises and after landing during dynamic balance exercises. The unsupervised sessions for the FIRE intervention will consist of single-limb balance, triceps surae stretching, supination and pronation resistance band, and intrinsic foot muscle exercises. Additionally, plantar massage will be self-administered by rolling the plantar surface of the foot on a textured massage ball on the ground [50].

### Outcome measures

Separate members of the study team who are trained in the assessments, demonstrated proficiency during pre-collection calibration, and blinded to group assignment will collect all outcomes. Blinding of the assessors will be maintained for the duration of data collection to avoid bias throughout the study timeline. The schedule for the collection of each outcome measure can be found in Fig. 1. Details of the outcome measures are included below.

### Primary outcomes

#### Recurrent ankle sprain and episodes of giving way

The number of recurrent ankle sprains since the previous testing session and the average number of ankle giving way episodes per week over the past month will be assessed through self-reporting. An ankle sprain will be operationally defined as an incident in which the rearfoot was inverted or supinated and resulted in a combination of swelling, pain, and time lost or modification of normal function for at least one day [37]. Episodes of giving way will be operationally defined as an incident in which the rearfoot suddenly rolled, felt weak, or lost stability; however, the individual will not have sustained an ankle sprain and was able to continue with normal function.

### Cumberland ankle instability tool

The Cumberland Ankle Instability Tool is a 9-item instrument used to identify self-reported impairments associated with CAI [51]. This instrument is scored on a 0–30 scale, where lower scores represent greater severity of CAI related symptoms [51]. The questions encompass various impairment areas associated with CAI including ankle pain, frequency of feeling unstable during activity, ability to control moments of instability, and perceived recovery time from episodes of instability. In development, this instrument demonstrated acceptable construct validity, internal reliability, test–retest reliability (ICC = 0.96), and could effectively discriminate between patients with and without CAI [51].

### Secondary outcomes

#### Static balance

Static postural control will be assessed with the Accusway Plus force plate (AMTI; Watertown, MA). Force and moment signals will be sampled at 100 Hz and converted to center of pressure estimates through Balance Clinic Software (AMTI, Watertown, MA, USA). Center of pressure data will be subsequently low-pass filtered at 5 Hz (Butterworth, 4th order, zero lag) through the Balance Clinic Software. Patients will perform one practice trial and three analysis trials of single-limb stance on each limb with eyes open and eyes closed for 20 s, for a total of 12 analysis trials. Patients will be instructed to stand with their arms folded across their chest, the uninvolved limb lifted off the force plate, positioned at approximately 45° of knee flexion, and the hip flexed to approximately 30°. If the patient touches down with the suspended limb, opens their eyes during eyes closed testing, or is unable to maintain the standing posture for the 10 s duration, the trial will be discarded and repeated. Center of pressure data will be separated into anterior–posterior (AP) and medial–lateral (ML) components and analyzed as AP and ML velocity, area 95% eclipse, and time-to-boundary (TTB) using a custom MATLAB code (The Mathworks, Natick, MA, USA) [42].

### Star excursion balance test

The Star Excursion Balance Test will be used as a clinical assessment to measure dynamic postural control. To complete this test, patients will place hands on hips, balance on the involved limb and reach with the uninvolved limb in the anterior, posteromedial, and posterolateral directions as far as possible. Trials will be discarded and repeated if the patient fails to maintain balance, lifts the heel, removes hands from hips, places weight on the reaching limb during toe touch, or fails to return to the starting position. Patients will complete four practice and three analysis trials in each direction on both limbs [52]. Collection trials will be averaged and normalized to leg length. Longer reach distances will represent greater dynamic postural control.

### Hop-to-stabilization

Dynamic postural control will also be measured using a forward jump hop-to-stabilization task [53, 54]. To complete this task, patients will initiate a double-leg forward jump and land on a single-leg. Patients were instructed to jump over a 30 cm hurdle placed at half the distance from the starting position to the target landing area (60 cm × 90 cm). The minimum jump distance (starting line to target landing area threshold) will be normalized to 40% of the person’s height. Patients will be instructed to land, obtain their balance, place their hands on the hips, and remain as still as possible for five seconds. Three successful trials will be recorded. Trials will be repeated if they do not land completely in the target area, touch down with the other foot, or move the stance leg after landing. Prior to beginning the task, an inertial measurement unit (Xsens DOT, V2.0.0, Xsens Technologies B.V., The Netherlands) will be secured to the low back (L4/5). Tri-axial acceleration data from this sensor will be sampled at 60 Hz. Using a custom MATLAB code (The Mathworks, Natick, MA, USA), dynamic postural stability index values will be estimated as the root mean square for accelerometer data in each orthogonal direction (AP, ML, Vertical) and resultant magnitude.

### Ankle and toe strength

Muscle strength will be assessed with the MicroFET2 digital handheld dynamometer (Hoggan Scientific LLC, Salt Lake City, UT, USA) using previously described methods [55]. Briefly, ankle dorsiflexion will be assessed in the longsit position with the dynamometer placed over the dorsal metatarsal heads. Ankle inversion and eversion will be assessed in the longsit position with the dynamometer placed on the medial and lateral forefoot, respectively. Ankle plantarflexion will be assessed with the patient laying prone and dynamometer placed on the plantar metatarsal heads. Lastly, the hallux and lesser toe flexion will be assessed with the patient’s forefoot suspended off the table with their heel flat and the dynamometer placed under the hallux or lesser toes. Strength measures will be based on a single trial of a “make test” and reported in Newtons (N). In the case of an invalid trial (due to equipment difficulty, deviation from test position, or compensatory motion), the patient will be allowed rest prior to retesting to mitigate effects from fatigue.

### Intrinsic foot muscle activation

Abductor hallucis, flexor digitorum brevis, quadratus plantae, and flexor hallucis brevis thickness and functional activation ratios will be captured using ultrasound imaging and measured using WebPlotDigitizer software version 4.6 (Ankit Rohatgi, https://automeris.io/WebPlotDigitizer, Pacifica, CA, USA). The patient will be positioned supine with the plantar aspect of the foot exposed. The shank will be secured to a bolster to standardize patient positioning. The assessor will ensure both the forefoot and rearfoot are neutrally positioned in both sagittal and frontal planes during scanning. The ultrasound transducer placement will be standardized based on a previously described protocol [56]. The gain will be adjusted to ensure fascial borders of the IFM are identifiable. Initial measurements will be taken at rest with no contraction of the IFM. These measures will be followed by open kinetic chain isometric contractions of hallux abduction for the abductor hallucis (resistance applied at medial distal phalanx), lesser toe flexion for the flexor digitorum brevis and quadratus plantae (resistance applied at distal pads of toes 2–5), and hallux flexion for the flexor hallucis brevis (resistance applied at distal pad of great toe). Thickness measurements will be taken at rest and while activated based on previously described procedures [56]. The functional activity ratio will be calculated to measure IFM activation. An activation ratio of > 1.00 will indicate an increase in muscle size and < 1.00 will indicate a decrease in muscle size. This protocol has previously documented excellent reliability for these measures (ICC ≥ 0.87) [56].

### Plantar cutaneous sensation

Plantar cutaneous sensation will be tested using a 20-piece Semmes–Weinstein Monofilament kit (Touch-Test Sensory Evaluator; North Coast Medical, Gilroy, CA, USA) which has monofilaments ranging from to 0.008 g (1.65 level) to 300 g (6.65 level). Light touch detection thresholds will be assessed on the plantar surface at the 1st metatarsal head. Patients will lay prone with noise reducing headphones and asked to respond “yes” when they perceive a monofilament. Monofilaments will be applied perpendicular to the skin with the fiber bent to a “C” shape. Detection thresholds will be identified using a previously established 4–2-1 stepping algorithm method [57]. The detection threshold will be the lightest weight monofilament perceived by the subject. This protocol has demonstrated acceptable intrarater (ICC = 0.61–0.85) and interrater reliability (ICC = 0.62–0.92) [57].

### Foot and ankle ability measure

The Foot and Ankle Ability Measure is a region-specific patient-reported outcome used to assess functionality in patients with leg, ankle, or foot pathology with questions pertaining to the patient’s function level while performing activities of daily living and sport-related activities. The activities of daily living and sport subscales contain 21 items and 8 items respectively, and each scale is scored independently [58]. Each item is scored on a 5-point Likert scale where 0 indicates “*no problem*” and 4 indicates *“unable to do*”. The final score is often reported as a percentage of the total score, where lower scores indicate decreased self-reported function. The Foot and Ankle Ability Measure is reliable, valid and responsive in quantifying progress of patients with a wide range of foot and ankle pathologies [58]. Test–retest reliability is acceptable for both the activities of daily living (ICC = 0.89) and the sport (ICC = 0.87) subscales [58]. The minimal detectable change for the activities of daily living scale and sport subscales are ± 5.7 and ± 12.3 points, respectively [58].

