### Modified disability in the physically active scale

The Disablement in the Physically Active Scale (DPA) [59] is a generic 16-item patient-reported outcome instrument that assesses physical and psychosocial status for physically active adults. A modified version of this instrument was restructured to separate the items into a psychosocial (Mental Composite Score) and a physical component (Physical Composite Score) [60]. Each item is scored on a 4-point Likert scale with 0 indicating *no problem* and 4 indicating *severely affected*. Although the items are the same as the original, the two components are scored independently. Thus, the Physical and Mental Composite Scores range from 0 to 48 and 0 to 16, respectively, with higher scores indicating greater disability. Adequate internal consistency was demonstrated for both the Physical (*α* = 0.941) and Mental Composite Scores (*α* = 0.878). The minimal detectable change scores of the Physical and Mental Composite Scores in individuals with CAI is 7 and 3 points, respectively [23].

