### Fear avoidance beliefs questionnaire

The Fear-Avoidance Beliefs Questionnaire-Physical Activity subscale is designed to assess fear avoidance beliefs associated with physical activity in patients who are injured or who have a history of injury. This is a 5-item instrument scored on a 7-point scale with responses ranging from ‘*completely disagree*’ to ‘*completely agree*’. Scores range from 0 to 24 with a higher score representing increased fear avoidance [61]. This instrument has previously demonstrated sound clinometric properties including strong internal consistency and test–retest reliability (*a* = 0.77–0.96) with a minimal detectable change of 4 points in those with CAI [62, 63].

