### Power analysis

The primary comparisons for all aims are the comparisons between FIRE and SOC groups at 6 months for the CAIT (Aim 1), posteromedial reach direction of the SEBT (Aim 2), and the Foot and Ankle Ability Measure Sport (Aim 3). A two-sample t-test comparing the change score between the FIRE and SOC groups will have at least 95% power to detect an effect size of 0.6 between the group means when the sample size is 150 (75 per group), assuming a two-sided significance level of 0.05. In the case that attrition reaches 40%, the sample size will still allow for 80% power to detect the same effect.

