### Statistical plan and data analysis

Continuous variables will be summarized with descriptive statistics and categorical variables will be summarized with counts and percentages. Change scores and percent change scores will be calculated from baseline for follow-ups at post-intervention, 6-, 12-, and 24-months; the primary outcome for all aims is the 6-month change score. Simple comparisons between groups will be performed using two-sample t-tests for continuous variables and chi-square tests of independence for categorical variables. Effect sizes will be interpreted as weak (≤ 0.39), moderate (0.40–0.69), or strong (≥ 0.70). A two-sided significance level of 0.05 will be used for all statistical tests. All analyses will be completed with SAS v9.4 (SAS Institute, Cary, NC, USA).

Although groups will be randomly assigned, potential covariates will be examined with bivariate analyses, and comparisons requiring covariate adjustment will use regression modeling (e.g. ANCOVA, logistic regression); unadjusted and adjusted estimates will be presented with 95% confidence intervals. Potential covariates include: baseline outcome values, demographic variables (e.g., sex, age, height, weight, data collection site), prognostic indicators (e.g., number of previous ankle sprains, frequency of episodes of giving way, Identification of Functional Ankle Instability score), and intervention compliance (% sessions completed).

To examine the trajectory over time and whether the groups change differently over time, mixed model approaches may be used. Comparisons between groups, time points, and the interaction of group and time will be made using linear mixed models or generalized linear mixed models, as appropriate. Mixed model analyses allow for a repeated measures approach with flexibility in variance–covariance structure while also providing estimates in the presence of potential covariates. Unadjusted and adjusted estimates will be provided by condition and time; significant group-time interactions will allow for presentation of results by condition for each time point. While the primary analyses across all aims will be the comparison of group means, the analyses for Aim 1 will additionally include the estimation of recurrent ankle sprain rates at 6, 12, and 24-months for the FIRE and SOC conditions. Moreover, time to recurrent injury will also be examined.

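### The FAAM item anchors run opposite to the stated score direction, so the written scoring rule for the Aim 3 primary comparison is inconsistent; the FABQ-PA and mDPA descriptions need minor corrections

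*Protocol article*

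**What the plan says.** **FAAM.** The section on this measure says: "Each item is scored on a 5-point Likert scale where 0 indicates" no problem, with 4 at the other end for unable to do. It gives 21 items for activities of daily living and 8 for Sport. It then says: "The final score is often reported as a percentage of the total score, where lower scores indicate decreased self-reported function". No reverse scoring is mentioned. The detectable changes are ±5.7 points for daily living and ±12.3 for Sport.

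**Role in the trial.** The Power analysis section lists, among the primary comparisons at 6 months, "posteromedial reach direction of the SEBT (Aim 2), and the Foot and Ankle Ability Measure Sport (Aim 3"). The Statistical plan adds that "the primary outcome for all aims is the 6-month change score" and that percent change from baseline will also be calculated. All tests are two-sided at 0.05.

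**FABQ-PA.** The section states: "This is a 5-item instrument scored on a 7-point scale". It then states: "Scores range from 0 to 24 with a higher score representing increased fear avoidance". The detectable change is 4 points.

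**mDPA.** The section states: "Each item is scored on a 4-point Likert scale with 0 indicating" no problem and 4 indicating severely affected. There are 16 items, the composites run 0 to 48 (Physical) and 0 to 16 (Mental), and the detectable changes are 7 and 3 points.

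**The concern.** Consecutive statements about the FAAM cannot both hold unless something unstated happens between them. The anchors make a higher item score worse, while the interpretation makes a higher total better. A programmer who sums the printed codes, and an analyst who reads the result as printed, would credit the benefit to the wrong arm.

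This matters because FAAM Sport carries the Aim 3 primary comparison, in a superiority trial whose hypothesis is directional: FIRE is expected to reduce self-reported disability beyond SOC. Table 1 gives first enrolment as October 2021 and the status as recruiting, so data may already have been scored.

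The FABQ-PA and mDPA descriptions each contain a smaller mismatch between response scale and stated range or label. Neither is a primary comparison for any aim.

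**Working it through.** **1. The plan's power figures.** With effect size 0.6 and two-sided 0.05, the two-sample t-test has 95.5% power at 75 per group (95.7% by normal approximation). After 40% attrition, 75 × 0.6 = 45 per group, it has 80.4% (81.2%). Both stated figures reproduce, and nothing below changes them.

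**2. FAAM Sport from the printed anchors.** Score = 100 × (sum of items) / (8 × 4), with maximum 32.

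| Patient | Sum | Score by printed codes | Stated reading of that score |
|---|---|---|---|
| No problem on all items | 0 | 0/32 = 0% | worst function |
| Unable to do on all items | 32 | 32/32 = 100% | best function |

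The daily-living subscale behaves the same way (21 × 4 = 84; 0% and 100%). The two statements agree only if the anchors are swapped or the score is taken as 100 minus the percentage.

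**3. Effect on the change score.** Let S be the score with higher meaning better, and P = 100 − S the score from the printed codes. Each patient's change is P6 − P0 = −(S6 − S0). The difference in mean change between arms therefore flips sign and the standard deviations are unchanged. A true benefit of +0.6 SD appears as −0.6 SD, while |t|, the two-sided p-value and |effect size| stay the same. One simulated data set, with assumed mean changes of 19 and 10 points, SD 15 and 75 per arm, gave t = 4.504 and t = −4.504 under the two codings, each with p = 0.000013.

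**4. Effect on percent change.** This summary divides by the baseline, so the reversal does more than flip the sign. Illustration with assumed scores:
- Higher is better, 70% to 85%: 15/70 = +21.4%.
- Same patient by the printed codes, 30% to 15%: −15/30 = −50%.

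A patient reporting no problem on any item at baseline has P0 = 0, so percent change is undefined.

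**5. FABQ-PA.** Five items on seven points give 0 to 30 (coded 0 to 6) or 5 to 35 (coded 1 to 7). Neither is 0 to 24, and 24/5 = 4.8 is not a possible item maximum. Four items coded 0 to 6 give 4 × 6 = 24, but no such rule is stated.

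**6. mDPA.** Codes 0 to 4 are five levels. The ranges fit them: 48/4 = 12 items and 16/4 = 4 items, and 12 + 4 = 16, the stated number. A 0 to 3 coding does not fit, since 16/3 is not a whole number of items. Only the 4-point label is wrong.

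**The case against.** The strongest reply is that the article gives no scoring formula. The percentage sentence describes how the instrument is often reported, and the intended direction, lower is worse, is explicit. A reversed result needs two steps: summing the raw printed codes without recoding, and then reading the total by the stated direction. Nothing shows that the trial does this. That stands, and it makes the reversal a conditional risk. A reader might infer that the Aim 3 result will come out with the wrong sign; the document does not support that.

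A reader might also infer that the Aim 3 test or sample size is compromised. It is not, because a pure reversal leaves two-sided inference on the change score unchanged (step 3). Nor do the quoted detectable changes generally lose their meaning. The FAAM values are symmetric, so reversing a percentage scale does not alter them. The mDPA values sit on ranges that agree with the item codes. Only the FABQ-PA value of 4 points rests on an unresolved scale.

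Calling all three scoring rules impossible would go too far. The mDPA error is a label. The FABQ-PA range is unreachable only if all five items are summed, and an unstated four-item rule would reconcile it.

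Finally, the FAAM is described under Secondary outcomes, and the outcomes listed as primary are sprains, giving way and the Cumberland tool. That is correct, but the Power analysis section still makes FAAM Sport the primary comparison within Aim 3. Item-level scoring may be left to a fuller document, but that does not excuse two printed statements that conflict.

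**Conclusion.** The point holds for the FAAM. As printed, the item coding and the interpretation of the Aim 3 primary comparison contradict each other, and the text offers nothing to reconcile them.

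The consequence, if both statements are followed literally, is a reversed favoured arm on the 6-month change score and percent-change summaries altered in size as well as sign. Power, absolute effect size and two-sided p-values for the change score do not move. This assumes that every patient is scored the same way; the document does not show which coding is in use.

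The FABQ-PA mismatch is real but minor, as it concerns a measure that is not a primary comparison. The mDPA mismatch is one word, with no numerical effect.

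**What to change.** - **FAAM:** make anchors and direction agree. Either swap the anchors, so that 4 is no problem and 0 is unable to do, or keep them and state that the score is reversed. In both cases state that higher means better function.
- **Verification:** before analysis, confirm that the data-entry forms (including electronic follow-up), the scoring code and the data already collected at the three sites follow that direction. One check is that a patient with no problem on any Sport item scores 100%.
- **FABQ-PA:** state how many items are scored and how they are coded, so that they match the stated 0 to 24 range and the 4-point detectable change. The document gives no basis for changing the range instead.
- **mDPA:** replace the 4-point label with 5-point (0 to 4).

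The cost is a few lines of wording and a check of the scoring code. Design, sample size and patient burden are unaffected.
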